## Abstract

**Background:**

There is a need for psychosocial interventions for men with prostate cancer to promote adaptive coping with the challenges and distress associated with diagnosis, treatment and recovery. In addition, interventions are needed that help to overcome barriers to psychosocial treatment such as limited face-to-face psychosocial support services, a shortage of adequately trained professionals, geographical distance, perceived and personal stigma and a preference for consumer-centric and self-directed learning. *My Road Ahead* is an online cognitive behaviour therapy (CBT) intervention for prostate cancer. This protocol describes a randomised controlled trial (RCT) that will evaluate the efficacy of this online intervention alone, the intervention in combination with a moderated online forum, and the moderated online forum alone.

**Methods/design:**

This study utilises a RCT design with three groups receiving: 1) the 6-module My Road Ahead intervention alone; 2) the My Road Ahead intervention plus a moderated online forum; and 3) the moderated online forum alone. It is expected that 150 men with localised prostate cancer will be recruited into the RCT. Online measures will assess men’s psychological distress as well as sexual and relationship adjustment at baseline, post-intervention, 3 month follow-up and 6 month follow-up. The study is being conducted in Australia and participants will be recruited from April 2012 to Feb 2014. The primary aim of this study is to evaluate the efficacy of My Road Ahead in reducing psychological distress.

**Discussion:**

To our knowledge, My Road Ahead is the first self-directed online psychological intervention developed for men who have been treated for localised prostate cancer. The RCT will assess the efficacy of this intervention in improving psychological well-being, sexual satisfaction, relationship satisfaction and overall quality of life. If successful, this intervention could provide much needed support to men receiving treatment for localised prostate cancer in a highly accessible manner.

**Trial registration:**

Australian New Zealand Clinical Trials Registry Identifier: ACTRN12611000278932

### Psychosocial interventions for men treated for localised prostate cancer

The efficacy of psychosocial support has been repeatedly reported in the general cancer setting. Unfortunately, access to evidence-based and timely psychosocial support is often limited, particularly in rural and remote regions of Australia but also in public hospitals across the country and, indeed, worldwide. It has been reported that only 14 to 21% of Australian women with cancer attend face-to-face support [16,17]. Men are lower utilisers of health services in general [18] and international reports indicate that mental health service utilisation by men is lower than women [19].

A recent systematic review of psychosocial interventions for men with prostate cancer and their partners highlighted the poor quality of current research in this field [20]. The authors concluded that group cognitive-behavioural and psycho-educational interventions with a specific focus on cancer specific distress show the most robust research evidence for efficacy, however, further research is required [20]. Another review explored psychosocial interventions addressing sexual or relationship functioning in men treated for prostate cancer [21]. This review concluded that there is some evidence to support the efficacy of psychosocial interventions in improving sexual functioning especially when delivered face-to-face or through utilisation of complex interventions that specifically target sexuality and the relationship. However, this review also concluded that further research is required [21]. Related to sexuality and intimacy, masculinity is emerging as an important area [22] and yet it is not routinely addressed and integrated into interventions.

### Online interventions

Mental and behavioural health promotion, prevention, treatment and management-oriented interventions that are delivered via the internet or other electronic technologies, with or without human support [23], often referred to as “e-Interventions”, can overcome many barriers of access that are commonly encountered in our healthcare system. Whilst the use of e-Interventions has grown in both the mental health and general health setting [24-26] it has received limited attention in the cancer setting.

In the cancer setting, most online research has focused on developing and evaluating online peer support interventions with mixed outcomes in female cancer samples [27-29]. van den Brink [30] developed an online information and support intervention for head and neck cancer patients in the Netherlands with the aim of overcoming the communication and information bottlenecks in supportive head and neck cancer care. The authors reported that patient use and satisfaction with the intervention was very high despite patients having recently undergone intensive surgical treatment. Patient age was not a barrier (mean age 59 years and range 38-78) and, despite 56% of participants having limited computer experience prior to the use of the intervention, consistently positive feedback was received. This online support intervention showed improved QoL outcomes in participants as compared to those in a control group who did not access the intervention [30]. However, the intervention focused on psycho-education and support rather than skills in coping with the experience of cancer diagnosis, treatment and recovery.

Schover et al. [31] developed and assessed the efficacy of an online sexual counselling intervention in comparison to traditional face-to-face sexual counselling for couples following treatment for localised prostate cancer. Sexual counselling involved three face-to-face sessions with a therapist while the online intervention delivered the therapy via email contact with a therapist. This study found that the delivery of the intervention via the internet was as effective as the traditional face-to-face intervention in producing enduring improvements in sexual outcomes [31]. While this study highlighted the potential utility of online interventions in this population, to date, no online self-directed intervention with minimal support and a focus on a range of identified problem areas has been developed and evaluated for localised prostate cancer.

A recent review by Leykin et al. [32] explored the role of online interventions in supporting people with cancer. This review highlighted that e-Interventions can provide the majority of people with an acceptable alternative support modality in a systematic and scalable way. Research has found that telephone and internet-based support is particularly important for men with cancer, predominately prostate cancer, living outside metropolitan regions in Australia [33]. Psycho-education and self-directed therapeutic techniques can easily be transferred to an online environment and may also break down the barriers that many people face in terms of accessing support, including lack of available resources and perceived and personal stigma, fear and uncertainty in accessing mental health services [32,34]. Leykin et al. [25] criticised current online resources for being predominately information and support based, with a need for evidenced-based treatment interventions.

The current study involves a randomised controlled trial (RCT) assessing the effectiveness of three online interventions: (i) access to an online intervention program (My Road Ahead-only); (ii) access to the online intervention plus to a moderated online forum (My Road Ahead-plus-forum); and (iii) access to the online form only (forum-only). This study design was chosen to evaluate the online intervention in comparison to a more basic level of care (some peer support) and to separate the effect of the online intervention and the peer support forum on treatment outcomes. Past RCTs have used a variety of control conditions from wait-list control groups, care as usual, or some basic information provision. Cuijpers et al. [35] have criticised past internet-based RCTs for failing to use control groups beyond a wait-list control, since there may be an overestimation of intervention efficacy when those in a wait-list control condition are unlikely to make self-directed steps to improving their situation if they are “waiting”. A web-based comparative condition has been recommended to overcome these problems [36]. Basic moderated forums have been used in previous studies as a control group as a means to control for spontaneous improvement or to control for the general attention and the possible beneficial effects from sharing one’s experience with others (e.g. [37,38]). In addition online support groups may themselves have positive effects for people with cancer (e.g., [28,29]), and the use of three groups would allow for exploration of the relative benefits of the online psychological intervention and peer support (forum).

## Method/design

### Aims and hypotheses

The overall aim of the RCT is to examine the efficacy of the online, self-directed, psychological intervention, *My Road Ahead* alone versus My Road Ahead plus use of a moderated online forum, versus the forum alone in improving participants’ psychological distress as well as sexual, relationship and psychosocial adjustment from baseline to post-intervention, 3 months and 6 months follow-up.

Primary outcome:

Psychological distress as measured by the combined total score of the DASS-21 will be used as the primary outcome measure.

It is hypothesised that:

1. Participants randomised to receive My Road Ahead, with or without access to the forum, as compared to those who receive access to the forum only condition, will demonstrate significantly greater reductions in psychological distress from pre- to post-intervention and at 3 and 6 month follow-up.

2. Participants randomised to receive access to the moderated forum in addition to My Road Ahead, as compared to those who receive access only to My Road Ahead, will demonstrate significantly greater reduction in psychological distress from pre- to post-intervention and at 3 and 6 month follow-up.

Secondary outcomes:

It is hypothesised that:

1. Participants randomised to receive My Road Ahead, with or without access to the forum, as compared to those who receive access to the forum only condition, will demonstrate significantly higher quality of life as evidenced by measures of sexual adjustment, sexual confidence and satisfaction, masculine self-esteem, marital adjustment, relationship conflict and relationship communication style from pre- to post-intervention and at 3 and 6 month follow-up.

Mediation and moderation effects:

It is hypothesised that:

1. Intervention driven reductions in psychological distress will be mediated by masculine self-esteem and moderated by sexual confidence and relationship communication style.

### Study design

This study is registered with the Australian New Zealand Clinical Trials Registry; Identifier: ACTRN12611000278932. Ethical approval to conduct the study has been obtained from Melbourne Health, Swinburne University of Technology, Deakin University and Peter MacCallum Cancer Centre Human Research Ethics Committee’s. CONSORT [39] requirements for RCTs will be adhered to throughout the study.

### Procedure

Participant consent will be obtained using an online consent process. The consent form is provided to the participant in PDF format. Participants are asked to confirm that they understand the study conditions, that they have received a copy of the participant information and that they consent to take part in the study by selecting three check-boxes during the consent process. Participants will then move on to create a personal, password protected account on the My Road Ahead website and complete the baseline questionnaires. After completing the baseline questionnaires participants will then be randomly assigned using a computer generated sequential 1-to1- to 1 allocation across the three (3) groups. Participants and researchers involved in the management of the project are not blinded to the randomisation outcomes. Group 1 participants will receive access to My Road Ahead, the 6 module online program. Group 2 participants will get access to My Road Ahead plus access to the moderated forum. Group 3 participants will receive access to the moderated forum only.

Participants in all groups will receive a weekly email reminder to return to the program and/or forum and to encourage them to continue to participate in the research over the course of the 10 weeks of the intervention phase. Participants will also receive three reminder emails to complete the questionnaires at each time point.

Participants in all groups will undertake the online assessment at five time points; baseline, week 5, post-intervention (week 10 for group 3) and 12 weeks post intervention (week 22 for group 3), and 6 months post-intervention (see Figure 1).

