### Participants

A medium effect size is estimated for the primary outcome measure, total distress, as measured by the DASS-21 total score between groups across the five assessment points. To power the study at the 80% level, based on an alpha level of .05 with an estimated medium effect size (f = .25) and with three groups completing five assessment points, 125 complete responses will be required. To account for an estimated 20% drop-out rate a total of 150 participants will be required; 50 per group.

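### Five assessments are scheduled and powered but the aims name only four, with no stated role for week 5; separately, 150 enrolled with 20% loss gives about 78% power, not 80%

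*Protocol article*

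**What the plan says.** The protocol article gives two different sets of assessments for the same primary outcome, the DASS-21 total.

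- **Five occasions.** The Procedure section states: "Participants in all groups will undertake the online assessment at five time points; baseline, week 5, post-intervention", then 12 weeks and 6 months after the intervention. The Participants section describes the powered outcome "as measured by the DASS-21 total score between groups across the five assessment points" and concludes that "with three groups completing five assessment points, 125 complete responses will be required". It then allows for 20% dropout and arrives at 150 men, 50 per group.
- **Four occasions.** The abstract (Methods/design) places the measures "at baseline, post-intervention, 3 month follow-up and 6 month follow-up". Under Aims and hypotheses, the overall aim uses the same set. So does the first primary hypothesis, under which the My Road Ahead arms "will demonstrate significantly greater reductions in psychological distress from pre- to post-intervention and at 3 and 6 month follow-up" compared with forum-only. The second primary hypothesis, on adding the forum, uses the same time points.

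The Statistical analyses section names a repeated-measures MANOVA adjusted for age, then an intention-to-treat analysis and longitudinal hierarchical linear models. It does not give the number of occasions.

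**The concern.** Week 5 falls inside the 10-week intervention phase, so it cannot stand for post-intervention or follow-up. No primary hypothesis concerns it, yet the sample size counts it. If it enters the omnibus group-by-time test, that test has 8 numerator degrees of freedom instead of 6, and a significant result could reflect a mid-treatment difference about which the trial makes no claim. If the set of visits is not fixed, it can also be chosen after the data are seen.

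The second matter lies in the same Participants paragraph. The design target is "To power the study at the 80% level", with 125 completers. The 150 to be enrolled do not leave 125 completers if the stated 20% are lost, so the paragraph promises power that its own figures do not deliver.

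**Working it through.** **Inputs from the Participants section:** three groups (k = 3), five occasions (m = 5), alpha .05, power 80%, f = .25, 125 completers, 20% dropout, 150 enrolled. The analysis method, repeated-measures MANOVA, is from Statistical analyses. The four-occasion set (m = 4) is from the abstract and from Aims and hypotheses.

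**Assumption:** the article does not name the effect powered. I take it as the group-by-time interaction, with f read as f(V), the effect size on the Pillai scale.

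**Formula (Pillai approximation, noncentral F):**

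- s = min(k−1, m−1) = 2
- df1 = (k−1)(m−1)
- df2 = s(N − k − (m−1) + s)
- λ = s·N·f²

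**Step 1: reproduce the stated figure (m = 5).** df1 = 2 × 4 = 8. At N = 125, df2 = 2(125 − 3 − 4 + 2) = 240 and λ = 2 × 125 × 0.0625 = 15.625, which gives power 80.3%. At N = 124 power is 79.95%, so 125 is the smallest N that reaches 80%. This matches the article exactly.

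**Step 2: the dropout allowance.**

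- 125 × 1.2 = 150, the article's figure.
- 125/(1 − 0.20) = 156.25, so 157 enrolled are needed to leave 125.
- 150 × 0.80 = 120 completers.
- 150 enrolled leave 125 only if the loss is 25/150 = 16.7%.

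At N = 120 with m = 5, df2 = 230 and λ = 15.0, giving power 78.3%.

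**Step 3: the same formula with four occasions (m = 4).** df1 = 6. At N = 120, df2 = 2(120 − 3 − 3 + 2) = 232 and λ = 15.0.

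| Completers | Power, five occasions | Power, four occasions |
|---|---|---|
| 125 | 80.3% | 84.9% |
| 120 | 78.3% | 83.1% |

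At 125 completers both sets reach 80%. Power drops below 80% in this table only with five occasions and 120 completers, and it is the dropout inflation that takes the number from 125 to 120.

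**Step 4: sensitivity to the effect powered.** Suppose instead that a between-groups effect averaged over time was meant, with λ = f²·N·m/(1 + (m−1)ρ). The correlation ρ is not stated. With five occasions the required N is 96 at ρ = 0.5, 121 at 0.7, 124 at 0.73, 126 at 0.74 and 127 at 0.75, so this reading also gives about 125 for ρ near 0.73 to 0.74. At N = 125:

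| ρ | Power, five occasions | Power, four occasions |
|---|---|---|
| 0.5 | 90.1% | 88.8% |
| 0.7 | 81.7% | 80.9% |
| 0.73 | 80.4% | 79.7% |

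Under this reading the visit count moves power by about 1 point, in the opposite direction.

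**The case against.** The strongest reply is that the two operative sections, Procedure and Participants, agree on five. The hypotheses say when benefit is expected and are not a visit schedule, and an abstract may abbreviate. A mid-treatment measurement is legitimate in a longitudinal model, and its role may be given in the full protocol or in Figure 1, which is not shown. Much of this stands: scheduling week 5 is not an error, and no figure is miscalculated because of it. What remains is that the article powers its primary outcome on an occasion absent from every primary hypothesis and does not say whether that occasion is part of the test.

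Three stronger readings are tempting and are not supported:

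- **That the visit mismatch makes the trial underpowered.** At the stated 125 completers both visit sets meet 80%. Under the interaction reading, dropping week 5 raises power.
- **That the sample could be restated as 113 completers and 142 enrolled.** The interaction formula does give 113 for four occasions, and 113/0.8 = 141.25. But that rests on an inferred f(V), held at .25 after an occasion is removed, which need not be so. It would also justify a smaller trial for an omnibus test that is still not either hypothesised contrast. Under the between-groups reading, four occasions need slightly more men (126 against 124 at ρ = 0.73).
- **That a man who misses only week 5 is lost to the analysis.** This is true of a complete-case MANOVA. The hierarchical linear models that are also planned would keep him.

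**Conclusion.** The point holds in two separate parts.

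First, the article is inconsistent about which assessments make up the primary comparison: five in Procedure and Participants, four in the abstract and in Aims and hypotheses. The role of week 5 is not stated. The effect on power is modest, and its direction depends on the effect powered. From five occasions to four at 125 completers, power rises by 4.6 points for the MANOVA interaction and falls by about 1 point for a between-groups effect. The interaction reading is the better supported, since it gives 125 exactly without an assumed correlation and fits the named analysis, but it remains an inference.

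Second, the stated 80% power is not delivered by 150 men with 20% loss. The five-occasion test has about 78% power at the 120 expected completers, assuming f(V) = .25. The shortfall is about 2 points and is due to the dropout arithmetic, not to the number of visits.

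**What to change.** 1. **Primary test.** Test the primary hypotheses by contrasts at post-intervention, 3 months and 6 months. Keep week 5 as a process or mediation measurement outside those contrasts.
2. **Alignment.** Bring the abstract, Aims and hypotheses, Procedure and Participants into line, with one sentence on the purpose of week 5.
3. **Sample size.** Restate the Participants section as 120 expected completers from 150 enrolled, with about 78% power for the five-occasion test. If a four-occasion test is used, report power for that test (about 83% at 120 completers under the same f(V) assumption) and leave enrolment at 150. Name the effect powered and say how f is defined. Neither figure is the power of the individual contrasts, which needs its own calculation.

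The cost is wording in four places and a slightly less favourable stated power if five occasions are kept. No extra men or visits are needed.

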**Figure 1 F1:**
[figure not shown]
Flow chart of participant movement through RCT.

#### *Inclusion and exclusion*

Eligibility criteria include participants having been diagnosed with localised prostate cancer and have received treatment with curative intent (or currently receiving treatment) within the last 5 years. They must not have a diagnosis of advanced or metastatic disease. Participants must be able to utilise a computer or mobile device and have access to a connection to the internet at least once per week for up to one hour. They must be able to read, write and understand the English language without the assistance of an interpreter.

#### *Recruitment*

Participants will be recruited across Australia with advertisements published in various national and local newspapers as well as on various health websites (including the Prostate Cancer Foundation of Australia (http://www.prostate.org.au), beyondblue (http://www.beyondblue.org.au), MensShedOnline (http://www.theshedonline.org.au)). In addition participants will also be recruited via letters from urologists and radiation oncologists practising at the collaborating institutions including Royal Melbourne Hospital, Epworth Healthcare and Peter MacCallum Cancer Centre. Participants will be recruited across a variety of locations so as to maximise the recruitment of participants with a range of demographic variables.

#### *Randomisation*

Participant consent and sign up to the study is conducted entirely online and participants self-generate their username and password so as to ensure privacy and confidentiality. Randomisation is computer-generated on a sequential basis once the participant has completed the baseline questionnaire.

#### *My road ahead: the online psychological intervention*

My Road Ahead is a self-directed cognitive behavioural therapy (CBT) based intervention that provides psycho-education (through text, video, audio and graphics), a series of interactive exercises and regular automated feedback as participants progress through the program. The program features videos of real case experiences around coping with prostate cancer, as well as health professionals providing expert commentary.

The intervention is a six (6) module online program that offers a range of topics to work through at an individual pace across a period of ten (10) weeks. All modules are available to participants from the beginning and participants can use them in the order they chose, although a recommended sequence from 1-6 is suggested to participants.

Specific module themes are shown in Table 1.

**Table 1 T1:** Themes of the modules within the My Road Ahead intervention

**Module**	**Themes**
1. Prostate cancer and you	• Psycho-education about common emotional responses to prostate cancer
	• Normalisation through other men’s stories
	• Interactive reflective exercises aimed at encouraging self-reflection and acknowledgement of emotional responses
2. Effective communication	• Common communication challenges in context of prostate cancer
	• Strategies to improve general and relationship communication
	• Communication enhancement exercises to complete with partner or alone
3. Physical changes	• Common physical changes following treatment for localised prostate cancer
	• Exercises to overcome anxiety and avoidance in relation to incontinence
	• Introduction to relaxation strategies
4. Sexuality and masculinity	• Education and exercises targeting negative cognitions surrounding cancer and erectile dysfunction (ED)
	• Skills training in general and sexual communication
	• Education and exercises addressing masculinity and identity issues
5. Sexuality and intimacy	• Sexual problems and cancer
	• The impact of ED and cancer on the relationship
	• Education and exercises designed to broaden definitions of sexuality and sexual behaviour to enhance sexual intimacy
	• Education about the use of medical aids for ED
6. Planning for the future	• Education and exercises related to fear and uncertainty about the future
	• Planning for the future
	• Encouragement of continued use of the skills developed from the intervention

The intervention also includes weekly offline exercises that participants download and work through. Participants have the option to do these exercises alone or with their partner; completion of exercises with the partner is self-reported by participants at the post-intervention assessment. The program also includes a weekly mood monitor that generates a graph of mood status over the course of the intervention, a log book where men can record their responses to the exercises, and a bookmarking capability so men can return to pages of particular interest.

Moderated forum:

The two moderated forum facilities are also hosted on the website, however, participants who have access to the forum in addition to the My Road Ahead program will utilise a separate forum to those participants who only have access to the forum alone, to avoid contamination across groups. Both forums are moderated by the research team and offer a ‘virtual space’ for participants to ask questions of each other. The forum content is grouped by theme and participants are encouraged to log in at least once per week and contribute to the forum. The moderator posts a comment once per week to generate conversation. Data is collected about the number and frequency of forum posts for each user and qualitative analysis of the forums will be conducted at the conclusion of the study.

